#### Data Collection Procedures

Eligible participants will be notified via email and invited to attend 2 baseline in-person visits 1 week apart at the Curtin University study center. Before the first visit, participants will be asked to complete an online questionnaire (including ethnicity, education, employment, postcode, alcohol use, smoking, physical activity, eating and dietary habits, motivation, and weight loss history), as detailed in Table 1. At the baseline visit, participants will be asked to fast overnight before a blood test, whole-body composition dual-energy absorptiometry (DXA) scan, and height and weight measurement. They will receive training on how to record their dietary intake by taking images using the mFR app, a mobile app developed by Purdue University. The mFR app will be installed on participants’ mobile devices (Android [Google] or iPhone [Apple Inc]) at no cost. They will be asked to return approximately 1 week later, where they will receive a copy of their DXA scan and blood tests. They will be interviewed by the research dietitian to clarify the content of their mFR images and probe for missing data. Participants will undergo random allocation to the intervention or control groups. The assessments will be repeated for both groups at 6 and 12 months (Table 1). Participants will be asked to keep an adverse events diary (eg, hospital admissions, illness, or changes to medications) for the duration of the study that will be reviewed at the 6- and 12-month study assessment visits. Participants will be encouraged to discuss their involvement with their primary care doctor, who will be notified by the research team that their patient has volunteered and has been provided with blood test results, information about the trial, and contact details of the research team via a secure facsimile. Before each appointment, participants will be sent an email with details of their visit, along with a text message reminder the day before. Both intervention and control group participants will be provided with a study booklet with information on healthy eating from the Australian Dietary Guidelines (ADG) website [26]. This will include healthy eating information on food groups, serving sizes, links to recipes, and label reading.

**Table 1 table1:** Frequency of assessment variables for the chat2 (Connecting Health and Technology 2) study intervention and control groups.

Variables	Group	Baseline	6 months	12 months
Height and weight (measured at clinic visit)	I^a^ and C^b^	Yes	Yes	Yes
Body composition: whole body dual-X-ray-absorptiometry scan of regional or total body fat (including visceral body fat)	I and C	Yes	Yes	Yes
Adverse events diary	I and C	Yes	Yes	Yes
Dietary intake: 4-day mFR^c^	I and C	Yes	Yes	Yes
mFR usability to assess user feedback and method preference [14,27]	I and C	Yes	Yes	Yes
Blood sample: total cholesterol, triglyceride, LDL^d^ and HDL^e^ cholesterol, fasting glucose, and glycated hemoglobin	I and C	Yes	Yes	Yes
Health status EQ-5D, a 5-item scale to assess utility and health-related quality of life [28]	I and C	Yes	Yes	Yes
Sociodemographic and personal characteristics assessed via questions on sex, age, eating behavior, educational level, country of birth, ethnicity, socioeconomic status, and financial status	I and C	Yes	Yes	Yes
18-item Food Insecurity [29]	I and C	Yes	No^f^	No^f^
Self-report Habit Index Score [30]	I and C	Yes	Yes	Yes
Creature of Habit questionnaire [31]	I and C	Yes	Yes	Yes
Self-reported physical activity assessed via the International Physical Activity Questionnaire (short form) [32]	I and C	Yes	Yes	Yes
Depression, Anxiety, Stress Scale, with 21 self-report items to assess severity of depression, anxiety, and stress [33]	I and C	Yes	Yes	Yes
Weight-Loss History, an 8-item tool to assess previous weight-loss history [34]	I and C	Yes	No^f^	No^f^
The Health Care Climate Questionnaire [35]	I	No^f^	No^f^	Yes
Personalized Nutrition Questionnaire [21]	I	Yes	Yes	Yes

^a^I: intervention.

^b^C: control.

^c^mFR: mobile Food Record.

^d^LDL: low-density lipoprotein.

^e^HDL: high-density lipoprotein.

^f^Data not collected.

#### Dietary Assessment and Analysis

Participants will be provided with access to the mFR app on their mobile device to record their dietary intake at baseline, 6 months, and 12 months (Figure 2) [16,36]. They will be asked to take “before eating” and “after eating” images of all foods and beverages consumed over 4 consecutive days, including 1 weekend day. The mFR app communicates with a dedicated cloud-based server for the storage and processing of images via Wi-Fi or 4G and 5G networks. A fiducial marker is included in the image to allow improved accuracy for quantifying dietary intake [37-39]. The mFR app will be updated regularly in response to operating systems updates (Android and iPhone). Participants will label the content of their images, referred to as mini labels. When the participant starts typing the word, a list of foods will appear where they can select from a list of approximately 800 food and beverage items. These labels link to a food composition database (not visible to the participant) with the food code, detailed description, and energy and nutrient composition [40]. These mini labels will be linked to a code for estimating food group servings to enable a food-based assessment. At the study visit, the research dietitian will review the images with participants through the web and probe for food and beverage items not recorded (Figure 2). The data from the mFR will be entered into a purpose-built Microsoft Access database platform to assess the food group servings.

**Figure 2 figure2:**
[figure not shown]
Review process for viewing a labeled eating occasion, with colored labels identifying the foods and the time and date stamp displayed.

#### Diet Quality Scoring

Analysis of the 4-day mFR will be undertaken by the research dietitian, and a food-based diet quality score (DQS) will be calculated (Table 2). In addition to energy reduction, this study will assess diet quality, as there is emerging evidence that diet quality, particularly reduced ultraprocessed foods, have a role in energy balance [41,42]. The 11-component DQS is based on the ADG [26] and adapted from 2 food-based indexes developed for Australian adults [43,44]. The DQS uses a continuous weighting system based on increments of food group servings, or proportions of total intake for behaviors without set recommendations, such as variety of fruits and vegetables. For core food groups, such as fruits and vegetables, the maximum weighting assigned to the item is determined by the ADG-recommended daily servings. To achieve weight reduction consistent with study goals, discretionary foods and beverages will be split into separate components. Reverse scoring is assigned for discretionary (energy-dense and nutrient-poor) foods, sugar-sweetened beverages, and alcoholic beverages, where a maximum score of 10 points is achieved with zero servings. The DQS at baseline and 6 months will be provided to the study dietitians to be relayed to intervention group participants in the video consultations.

**Table 2 table2:** Diet quality scoring calculated from average daily servings based on the Dietary Guidelines for Australia. Total maximum score of 100 points from 11 components.

Item Description	Minimum score	Composite scores	Maximum score
Fruit	0 to <0.5 servings (0 points)	≥0.5 to <1.0 serving (2.5 points) ≥1.0 to <1.5 servings (5 points) ≥1.5 to <2.0 servings (7.5 points)	≥2 servings (10 points)
Vegetables and legumes or beans	0 to <1.0 serving (0 points)	≥1.0 to <2.0 (2 point) ≥2.0 to <3.0 servings (4 points) ≥3.0 to <4.0 servings (6 points) ≥4.0 to <5.0 servings (8 points)	≥5 servings (10 points)
Variety of fruits	0 type (0 points)	1 type (1 point) 2 types (2 points) 3 types (3 points) 4 types (4 points)	5 or more types (5 points)
Variety of vegetables	0 type (0 points)	1 type (1 point) 2 types (2 points) 3 types (3 points) 4 types (4 points)	5 or more types (5 points)
Lean meat, poultry, fish, eggs, nuts, seeds, legumes, or beans (women)	>2.5 servings or <0.5 servings (0 points)	≥0.5 to <1.0 (2 points) ≥1.0 to <1.5 (4 points) ≥1.5 to <2.0 (6 points) ≥2.0 to <2.5 (8 point)	2.5 servings (10 points)
Lean meat, poultry, fish, eggs, nuts, seeds, legumes, or beans (men)	>3 servings or <1.0 serving (0 points)	≥1.0 to <1.5 servings (2 points) ≥1.5 to <2.0 servings (4 points) ≥2.0 to <2.5 servings (6 points) ≥2.5 to <3.0 servings (8 point)	3 servings (10 points)
Milk, yoghurt, cheese, and alternatives	<0.5 servings (0 points)	≥0.5 <1.0 servings (2 points) ≥1 to <1.5 servings (4 points) ≥1.5 to <2.0 servings (6 points) ≥2 to <2.5 servings (8 points)	≥ 2.5 servings (10 points)
Grain (cereal) foods, mostly wholegrain, and high cereal fiber varieties	<1.0 serving or >6.0 servings (0 points)	≥1.0 to <2.0 servings (1 point) ≥2.0 to <3 servings (2 points) ≥3.0 to <4 servings (5 points) ≥4.0 to <5 servings (6 points) ≥5.0 to <6 servings (8 points)	6.0 servings (10 points)
Discretionary foods	≥2.75 servings (0 points)	≥1.75 to <2.75 servings (2 points) ≥0.75 to <1.75 servings (4 points) >0 to <0.75 servings (8 points)	0 servings (10 points)
Sugar-sweetened beverages	≥2 servings (0 points)	≥1.25 to <2 servings (2 points) ≥0.5 to <1.25 servings (4 points) >0 to <0.50 servings (8 points)	0 servings (10 points)
Alcoholic beverages	≥2 servings (0 points)	≥1.25 to <2 servings (2 points) ≥0.5 to <1.25 servings (4 points) >0 to <0.50 servings (8 points)	0 servings (10 points)
Plain water	<1 cup (0 points)	≥1 to 3 cups (2 points) ≥3 to 5 cups (6 points) ≥5 to <8 cups (8 points)	≥8 cups (10 points; women) ≥10 cups (10 points; men)

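### Table 2 gives full marks for protein foods and grains only at one exact average and zero just above it, and leaves some men's water intake unscored

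*Protocol article*

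**What the plan says.** Diet Quality Scoring, Table 2, sets the scale: "Diet quality scoring calculated from average daily servings based on the Dietary Guidelines for Australia", with "Total maximum score of 100 points from 11 components". The average comes from the mobile food record, which covers "all foods and beverages consumed over 4 consecutive days, including 1 weekend day" (Dietary Assessment and Analysis).

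The zero bands at issue are:
- protein foods, women: ">2.5 servings or <0.5 servings (0 points", with 10 points printed at 2.5 servings;
- protein foods, men: ">3 servings or <1.0 serving (0 points", with 10 points printed at 3 servings;
- grains: "<1.0 serving or >6.0 servings (0 points", with 10 points printed at 6.0 servings.

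The fruit, vegetable and milk rows instead have open-ended maxima (at least 2, 5 and 2.5 servings).

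For plain water the top intermediate band stops below 8 cups, and the maximum is "≥8 cups (10 points; women) ≥10 cups (10 points; men". The lower water bands share their edges at 3 and 5 cups.

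The text states the principle: "The DQS uses a continuous weighting system based on increments of food group servings, or proportions of total intake". It ties the core-group maximum to the recommended servings and names only discretionary foods, sugar-sweetened beverages and alcohol as reverse scored. The Statistical Analysis section lists change in DQS as a secondary outcome; the primary outcome is weight change at 12 months.

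**The concern.** A score meant to rise in increments toward the recommended amount should not collapse when a multi-day average passes that amount by a trivial margin. In these rows it does, and the full 10 points sit on a single value that an average of four days will seldom hit. Two people with nearly the same diet can differ by 8 or 10 points on one component. A person just over the target ranks below one eating a small fraction of it. Moving typical intake up to the target can lower the expected component score, so the component can fall while diet moves toward the guideline.

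For water the problem is different: the total cannot be computed as written for a man between 8 and 10 cups. Table 3 advises 8 to 10 cups, so a man acting on the trial's own advice can land there.

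**Working it through.** **1. The plan's own total.** Nine components with a maximum of 10 and two variety components with a maximum of 5, counting the protein row once per person: 9 × 10 + 2 × 5 = 100 over 11 components. This agrees with Table 2.

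**2. Printed bands applied literally.**

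| Row | Low intake | Just below target | At target | Just above |
|---|---|---|---|---|
| Protein, women | 0.5 → 2 | 2.49 → 8 | 2.50 → 10 | 2.51 → 0 |
| Protein, men | 1.0 → 2 | 2.99 → 8 | 3.00 → 10 | 3.01 → 0 |
| Grains | 1.0 → 1 | 5.99 → 8 | 6.00 → 10 | 6.01 → 0 |

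Each person has one protein row and the grain row, so at most 2 × 10 = 20 points are affected.

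**3. Water.** Men at 8, 8.5, 9 and 9.9 cups match no band; women at the same values score 10. For both sexes exactly 3 cups matches 2 and 6 points, and exactly 5 cups matches 6 and 8.

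**4. One person with true intake at the target.** The article gives no intake SD and no recording unit. Assumed: between-day SD 0.6 to 1.4 servings, days recorded to 0.25 serving.
- SD of the 4-day mean = SD/√4 = 0.3 to 0.7. Spacing of possible means = 0.25/4 = 0.0625.
- P(exactly on target) ≈ 0.0625/(SD of mean × √(2π)) = 0.0625/(0.3 × 2.507) = 0.083, down to 0.0625/(0.7 × 2.507) = 0.036.
- P(above target) ≈ (1 − 0.083)/2 = 0.458 to (1 − 0.036)/2 = 0.482. Simulation of 400,000 four-day means per case gives 46 to 49%.
- Expected score, women's protein: 3.6 to 4.4 at a true 2.5 servings, against 4.8 to 6.7 at 2.0. Men at 3 servings behave the same.
- Expected score, grains: 4.1 to 4.5 at 6 servings, against 5.8 to 7.6 at 5.5.

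**5. A group of people.** Averages assumed normal across people and rounded to 0.25 serving.
- Women's protein, SD 0.8: raising the mean from 2.0 to 2.5 lowers the mean component score from 4.9 to 4.1.
- Grains, SD 1.5: raising the mean from 5 to 6 lowers it from 4.9 to 3.8.
- With an open-ended maximum, the mean score at the target is about 8.5 in each of the three rows.

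**6. Sensitivity to rounding.** The article states no rounding rule. If averages were rounded to half servings, 26 to 45% of a group centred on target would still score 0 for excess (protein SD 0.4 to 1.2, grain SD 0.8 to 2.2). In the one-person case, a woman at 2.5 would still expect less than at 2.0 (5.3 to 7.6 against 6.4 to 7.9).

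**The case against.** An upper limit may be deliberate. This is a weight-loss trial, Table 3 tells participants to eat less at meals except for vegetables and salad, and the score is adapted from two published indexes that are not shown. Under such a limit, someone falling from 3.5 to 2.4 protein servings gains 8 points, so a loss above target is not always a wrong sign. This stands as a reason not to assume that the open-ended form was meant. It does not explain a drop from 10 to 0 over 0.01 serving, which the text does not describe. Nor is a lost ≥ sign a likely cause: the zero bands print >2.5, >3 and >6.0, so a ≥ maximum would contradict them.

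The size also rests on assumed SDs and recording units, and true intake placed exactly on the cut-point is the least favourable case. That is fair; the ordering in step 2 needs no such assumption.

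Other apparent faults carry little weight. Stepwise scoring fits a weighting built on increments. The uneven grain steps are a matter of choice. Gender other than man or woman can probably be handled, because sex is collected. The shared water edges touch only exact values and may be a slip in print.

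**Conclusion.** The point holds as a defect in a stated scoring rule, not as a missing detail. The protein and grain rows, up to 20 of 100 points, rank people just above target below people eating a fraction of it, and they conflict with the scoring principle in the same section. Men at 8 to under 10 cups have no total. The bands and the water gap are read directly from Table 2; the expected scores depend on the assumptions in steps 4 to 6.

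Four stronger readings are tempting and not supported:
- **That the trial's main result is at risk.** The DQS is secondary; the weight analysis and sample size are untouched.
- **That reaching the target costs points.** Hitting it exactly gains 2 points over the band below; only exceeding it loses them.
- **That 30 points can reverse for men.** Water has no upper penalty. Men in the gap are below the table's own 10-cup maximum, so their score is undefined, not reversed.
- **That the comparison of arms is biased in a known direction.** Only the intervention arm has the DQS relayed in consultations, but no effect on the total score, its SD, the difference between arms or power has been shown.

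**What to change.** Before the DQS is analysed, and before any comparison by arm:

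1. Reconcile the protein and grain rows with the stated principle. Either use an open-ended maximum, as for fruit, vegetables and milk, or, if an upper limit is intended, say so and use a maximum band with graded steps down.
2. Assign a score to men at 8 to under 10 cups, for example by continuing the 8-point band, and make the water bands non-overlapping.
3. Rescore baseline, 6 and 12 months from the stored food group servings with the same code.
4. Report the score as printed as a sensitivity analysis, with a stated convention for the undefined water values.

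The work is a change to scoring code on servings held in the study database. There are two costs. Analysed scores will differ from those already fed back, for some participants by up to 10 points per component. And recruitment ended in August 2024, so this is a late change to an outcome definition; it should be dated and explained, and the sensitivity analysis lets readers see its effect.

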#### Intervention Features

The intervention features, content, and behavior change techniques to be implemented are shown in Table 3. The selection of intervention features and strategies is guided by the COM-B model [18]. The COM-B model identifies behavioral targets when developing interventions and focuses on 3 factors required to change behavior: capability, opportunity, and motivation. Performing a behavior requires individuals to be capable or have physical and psychological abilities (eg, nutrition knowledge and cooking skills). Opportunity includes both practical and social aspects (eg, access to healthy foods, supportive environments, and social norms). Motivation comprises automatic drivers like habits as well as beliefs, emotions, impulses, and reflective processes such as intentions and planning. Behavior change techniques will include feedback, self-monitoring, feedback on performance, goals or planning, repetition, and substitution or habit formation [20].

**Table 3 table3:** Overview of the study goals and intervention features, content, and behavior change techniques.

Goal	How to achieve	Behavior change techniques [20]
1. Achieve a reduction in body weight by at least 5% in 12 months	Avoid or limit discretionary foods, sugary drinks, and alcohol Eating less at meals and snacks (except for vegetables and salad) Eating less often (avoid snacking—except for vegetables and salads)	Feedback—DQS^a^ from mFR^b^
2. Improve DQS	Eat from each of these five food groups with more variety (especially vegetables and fruit) every day Vegetables and legumes/beans, including different types and colors Fruit—choose fresh fruit as much as possible Grains (cereal) foods, mostly wholegrain and high cereal fiber varieties Lean meats and poultry, fish, eggs, tofu, nuts, and seeds, and legumes/beans (eg, kidney beans, chickpeas, lentils, and other beans) Milk, cheese, yoghurt, and alternatives, mostly reduced fat Drink more plain water (no added flavors); 2.1-2.6 L/day (8-10 cups)	Feedback and self-monitoring—DQS from mFR
3. Behavior change	Find your motivation Plan to make changes Set SMART^c^ goals Build healthy habits	Questionnaire for current barriers and enablers to eating behavior change and some goals (PNQ^d^) Goals and planning—action planning, commitment, goal setting, problem solving Goals and planning—action planning, commitment, goal setting problem solving, coping planning, implementation intentions Repetition and substitution—habit formation

^a^DQS: diet quality score.

^b^mFR: mobile food record.

^c^SMART: Specific, Measurable, Achievable, Relevant, and Time-Bound.

^b^PNQ: Personalized Nutrition Questionnaire.

#### Intervention Group

Participants allocated to the intervention group will be offered 8 video consultations (approximately 20 to 45 minutes based on intervention stage) with a dietitian for the first 6 months (at 2, 4, 8, 12, 16, and 24 weeks) to provide support and guidance for unhelpful behaviors (eg, emotional eating) and additional maintenance calls (relapse prevention and coping planning) at 9 and 12 months (8 in total). This number of individual contacts was chosen as a balance between recommendations [9] and practical service delivery costs. Before selecting telehealth consultations, participants complete the Personalized Nutrition Questionnaire (PNQ) to identify and prioritize self-perceived factors impacting on their eating behaviors [21]. The PNQ is a tool designed to support the dietitian during consultations by collecting information on barriers before the session. Based on the COM-B framework [18], the PNQ has been used with a variety of groups to support dietitian-led telehealth consultations [45-47]. The medical nutrition therapy consultation will cover dietary feedback focusing on their DQS, goal setting, and behavioral strategies. Feedback will be formulated from the analysis of the mFR and will focus on key dietary messages (Table 3). The content will address each participant’s personal barriers to changing dietary behaviors, reinforce capability, motivation, and guide adoption of health-enhancing habits.

#### Control Group

The control group will complete all measures and will be provided with a standard care study booklet using information from the ADG website [26]. At the end of the study, control group participants will receive personalized feedback on their outcomes, including their dietary feedback report.

### Dietetics Training and Consultations

Research dietitians will undertake 8 hours of in-person training, before their consultations with participants. The training will include approximately 2 hours of self-paced, recorded, online training in the dietitian’s own time and 6 hours of online or in-person workshops. The training will include current evidence-based practice for people living with obesity, addressing weight bias or stigma, study design, ethics, mFR technology or study systems, documentation, and fidelity of implementation adherence. Study dietitians will complete online training in motivational interviewing in health care [48]. The behavior change training conducted by the health psychology team will be guided by the COM-B model, and embedded with behavior change techniques [49]. A follow-up booster session will be conducted midway through the intervention. Standard guides will be developed for each of the 8 consultation sessions by the research team. Dietitians will use the consultation guide for each session, record attendance, and contact participants for missed sessions. The style of communication will be consistent with self-determination theory and motivational interviewing principles [15,50,51]. Fidelity of implementation adherence will be guided by a conceptual framework for implementation fidelity [52] (ie, adherence to the guide as prescribed and quality of delivery) and will be assessed for dietitians using measures of fidelity and engagement [53]. Practice management software for allied health professionals [54] will be used to manage appointments; send text appointment reminders; document attendance; record treatment notes; and access anthropometry, DQS, PNQ, and blood test results. Study dietitians will document each of the 8 sessions according to the nutrition care process: nutrition assessment, nutrition diagnosis, nutrition intervention, nutrition monitoring, and evaluation [55,56]. They will also document behavior change techniques implemented according to the COM-B model [20].

